	**Determine whether observed practice meets expected standards as defined by audit standards**			
		See Table 2		–
**Other objectives**				
	**Comparison of institutional factors and hepatobiliary services in hub and spoke centers**			
		**Institutional factors and HPB^m^** **services**		
			Hospital capacity	Number of inpatient beds
			Critical care capacity	Number of beds available for patients requiring intensive care or organ support Number of HPB surgical resections
			Interventional management of obstructive jaundice	Availability of biliary decompression services Number of decompression sessions per week
	**Assessment of data collection tools**			
		Hospital technological facilities		Proportion of sites with access to electronic reports of patient data
	**National research network development**			
		Promotion of collaborative research		Size of geographical region Number of sites in geographical regions Number of regional leads, local leads, and data collectors

^a^RICOCHET: Receipt of Curative Resection or Palliative Care for Hepatopancreaticobiliary Tumours.

^b^Hub-and-spoke design: network consisting of an anchor establishment, the hub, complemented by secondary establishments, the spokes.

^c^MDT: multidisciplinary team.

^d^USS: ultrasound scan.

^e^CT: computed tomography.

^f^MRI: magnetic resonance imaging.

^g^PET CT: positron emission tomography-computed tomography.

^h^EUS FNA: endoscopic ultrasound fine-needle aspiration.

^i^ERCP: endoscopic retrograde cholangiopancreatography.

^j^PTC: percutaneous transhepatic cholangiography.

^k^Successful decompression is defined as the successful deployment of a stent as stated on the latest procedure report.

^l^CNS: clinical nurse specialist.

^m^HPB: hepatopancreaticobiliary.

**Table 2 table2:** Audit standards of the RICOCHET^a^ study.

Audit standard		Standard compliance, %
Patients proceeding to surgery for pancreatic cancer should be found to have metastatic disease [9]		<25
For patients undergoing first biliary decompression, stent should be placed and cytology or histology taken where appropriate [18]		>80

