	**Intervention domains**			
		Biliary decompression		Utility: describing indication for decompression Modality: ERCP, PTC, or other Safety: decompression modality-specific complication rates Success rates as defined by successful biliary drainage^k^
		Neoadjuvant chemotherapy		Utility: rates of use Safety: chemotherapy-specific complication rates
		Nutritional supplementation		Utility of specialist nutrition team input: rates of referral Utility of pancreatic enzyme replacement: rates of prescription

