	**Intention domains**			
		Curative surgery		Time from presentation to surgery Rates of completion of surgery with curative intent or awaiting surgery Histological staging Rates of adverse events
		Palliative and end-of-life care planning		Rates of referral to hospital or community palliative care team if appropriate Number of patients seen by a CNS^l^ Number of patients where ceiling of care and resuscitation status has been discussed
		Other outcomes		Number of inpatient days Number of unplanned admissions Death: time and cause

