**Secondary objectives: nonresectable**				
	**Subgroup analysis of cohort who undergo biliary decompression^k^**			
		Management pathway, investigation, intervention, and intention domains		As in primary objective, with intention to determine associations with adverse events and “other outcomes”
		Additional intention domain: palliative chemotherapy		Rates of starting palliative chemotherapy

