**Patient survival after biliary decompression in palliative disease**		
	7 days [19,20]	>90
	30 days [21]	>75
Ability to proceed to palliative chemotherapy in patients with unresectable malignancy [22]		25

^a^RICOCHET: Receipt of Curative Resection or Palliative Care for Hepatopancreaticobiliary Tumours.

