## Discussion

Survival among patients with pancreatic cancer has not improved over the past 40 years, a fact that demands the attention of health care providers, users, and service designers [32,33]. Nevertheless, there are grounds for optimism. Adjuvant chemotherapy is increasingly effective, correction of pancreatic exocrine insufficiency can improve survival, and optimized diagnostic pathways can reduce the time to surgery and improve resection rates [9,34,35]. These are just a few examples of where progress is being made. Optimizing pathways, reducing variation in practice, and national guidance can all help achieve improvement. While more substantial improvements may occur from novel chemotherapeutics, it is clear that outcomes and patient experience can be improved by focusing on optimizing every part of the patient pathway, from diagnosis to treatment [36]. It is therefore essential that current practice and its variation and effect on patient outcomes are evaluated. This study closely follows the publication of the first NICE guidelines for the management of pancreatic cancer in the United Kingdom [16]. Real-world practice may stray from guidelines for a multitude of reasons, including limitations of local resources and expertise, case-specific vagaries, and, in some cases, perceived equipoise in the available data [9]. There may also be a tendency to overinvestigate patients, with consequent delays to treatment [10]. The RICOCHET study aims to reveal the main bottlenecks in the pathways and identify where improvements can be made.

The 15% of patients with potentially resectable disease are frequently the focus of clinical research, with a limited emphasis on the considerably larger proportion of patients with nonresectable disease [37]. The RICOCHET study is a comprehensive study of practice among all patients with suspected cancer, regardless of stage or treatment options. Analysis of Hospital Episode Statistics data demonstrates a remarkably high 30-day mortality rate among patients with malignant biliary obstruction, but the cause for this high incidence remains unknown [19]. A further benefit of the RICOCHET study is, therefore, to target areas where there is a particular need for more in-depth information.

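### Table 1 footnote k sets decompression success by the latest procedure report, so the status depends on survival and later procedures and should not be related to death as if known at the first procedure

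*Protocol article*

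**What the plan says.** All references are to the protocol article, Methods, Objectives.

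- **Definition.** Table 1, footnote k: "Successful decompression is defined as the successful deployment of a stent as stated on the latest procedure report".
- **Where it applies.** The footnote mark stands on the decompression outcome in the Intervention domains of Table 1, "Success rates as defined by successful biliary drainage", and on the heading of the nonresectable secondary objective, "Subgroup analysis of cohort who undergo biliary decompression".
- **What is done in that cohort.** All four domains are to be examined: "As in primary objective, with intention to determine associations with adverse events and" the items grouped as other outcomes. That group, in the Intention domains, includes "Death: time and cause".
- **The neighbouring audit standard.** Table 2 has its own stent standard, set at more than 80%: "For patients undergoing first biliary decompression, stent should be placed and cytology or histology taken where appropriate". Footnote k is not attached to Table 2.
- **Survival standards.** Under "Patient survival after biliary decompression in palliative disease", Table 2 gives more than 90% at 7 days and more than 75% at 30 days.
- **Horizon.** Case Identification, Inclusion, and Follow-Up makes 90-day outcomes from the first day zero the primary time frame.

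**The concern.** Success read from the latest report is not known at the first procedure. It is settled by what happens afterwards:

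- A patient whose first attempt fails and who dies before a repeat stays a failure.
- A patient whose first attempt fails, who lives to a repeat and is then stented, becomes a success.
- A patient stented at first whose later re-intervention fails becomes a failure.

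The first two rules move survivors out of the failure group. The third moves survivors into it. In each case the patient must be alive at the later procedure to change group. If the resulting label is then related to death counted from the first procedure, the comparison contains immortal time and need not be null when drainage success makes no difference.

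This matters most at 30 days in palliative biliary obstruction, which is where the authors want explanations. The Discussion says: "Analysis of Hospital Episode Statistics data demonstrates a remarkably high 30-day mortality rate among patients with malignant biliary obstruction", and presents the study as a way to obtain more detail there.

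A second, smaller matter is labelling. The latest-report rate is eventual success. It rises with each successful rescue and does not describe how often the first attempt works.

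**Working it through.** The article states no success rate, repeat rate or re-intervention rate for decompression, so there is no figure of its own to reproduce. What follows is an illustration. Time runs from the first procedure, and there is no true effect of success on death.

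**Inputs**

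- From Table 2: 30-day survival of 75%, the limit of the standard. With constant hazard, S(t) = 0.75^(t/30), so S(3) = 0.972, S(7) = 0.935, S(14) = 0.874, S(20) = 0.826 and S(90) = 0.422.
- Assumed: first-attempt success s = 0.80; repeat on day d = 3 to 14; share r = 0.5 to 0.7 of first failures alive at day d who are drained at the repeat.

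**Formulas**

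- Share of all patients moved from failure to success: (1 − s) × r × S(d).
- Latest-report success: s + (1 − s) × r × S(d).
- Deaths by day H among those moved: (1 − s) × r × (S(d) − S(H)).

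**Worked case: d = 14, r = 0.7, H = 30**

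- Moved: 0.20 × 0.70 × 0.874 = 0.122. Latest-report success is 0.922; failures are 0.078.
- Deaths among those moved: 0.20 × 0.70 × (0.874 − 0.750) = 0.0174.
- Mortality in failures: (0.20 × 0.25 − 0.0174) / 0.0776 = 0.420.
- Mortality in successes: (0.80 × 0.25 + 0.0174) / 0.922 = 0.236.
- Ratio: 0.420 / 0.236 = 1.78, where the truth is 1.00.

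**Adding late failures.** Suppose 15% of first successes alive at day 20 have a re-intervention and 20% of those fail (both assumed). Then 0.80 × 0.15 × 0.20 × 0.826 = 0.020 of all patients move from success to failure.

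| d, r | 30-day ratio, rescues only | 30-day ratio, with late failures | 90-day ratio, rescues only | 90-day ratio, with late failures |
|---|---|---|---|---|
| 3, 0.5 | 1.09 | 0.96 | 1.02 | 0.99 |
| 7, 0.7 | 1.44 | 1.18 | 1.10 | 1.04 |
| 14, 0.7 | 1.78 | 1.48 | 1.18 | 1.11 |

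With no repeats (r = 0) and no late failures the ratio is 1.00.

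**Second model.** A simulation used survival matched to both Table 2 limits (90% at day 7, 75% at day 30). First success was 75%, and 70% of surviving failures were re-attempted at day 7 with 80% success. By latest-report status, 30-day mortality was 23.8% in successes and 33.6% in failures. By first-procedure status it was about 25% in both. With the same late failures added, the latest-report figures became 24.1% and 30.3%.

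**Success rate.** In the first model, first-attempt success of 75% reads as 86% to 92% on the latest report, and 70% reads as 83% to 90%. For example, with s = 0.75, d = 14 and r = 0.5: 0.75 + 0.25 × 0.5 × 0.874 = 0.859. These figures are for stenting alone.

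**The case against.** The strongest defence is that the article nowhere says death will be compared by success status. The primary objective is descriptive, success is one of several decompression measures, and Statistical Analysis leaves methods open. Landmark or time-dependent handling is a detail an article may leave to an analysis plan. This stands in part: the comparison is implied by Table 1 and not named, and the absence of a method is no fault. But footnote k is a stated rule, and a plan that followed it would inherit a status fixed after the first procedure.

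Eventual drainage is also a sensible measure for a study that maps pathways from spoke to hub, since a failed spoke attempt rescued at the hub is a drained patient. That stands, and it is a reason to keep the measure under its own name.

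Four stronger readings are tempting, and the article does not support them.

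- **That Table 2 is contradicted.** It is not. Its standard concerns the first decompression and requires sampling as well as a stent where appropriate. Footnote k does not govern it, and it can be computed as written. Nor does the article say that the Table 1 rate is judged against 80%.
- **That the nonresectable cohort is limited to successful decompressions.** Only the position of the footnote mark suggests this. The heading speaks of patients who undergo decompression, which covers failed attempts.
- **That a failed endoscopic attempt rescued percutaneously is lost from the data.** Table 1 records modality and modality-specific complications. Whether success is held per procedure depends on a data form that is not shown.
- **That the distortion always makes failures look worse.** Late failed re-interventions work the other way, and the table above includes ratios just under 1.

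**Conclusion.** The point holds in a limited form. As defined, success status depends on survival to, and the result of, later procedures. It is unsuitable as a baseline characteristic when related to adverse events or death.

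Under the assumptions shown, the spurious risk ratio runs from about 1.0 to 1.8 at 30 days and from about 1.0 to 1.2 at 90 days, the study's primary time frame. The 1.8 needs every repeat at day 14, 70% of surviving failures drained, and no late failures. Every repeat and re-intervention input is assumed, so neither the size nor the direction can be known from the article.

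For description, the latest-report rate is valid as eventual success, provided it is labelled so and not set beside the Table 2 first-decompression standard. The change is worth making because it is cheap and bears on the 30-day mortality question that the authors single out.

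**What to change.** 1. For association analyses, define success as stent deployment stated on the first decompression procedure report.
2. Keep the latest-report measure as a separate descriptive outcome labelled eventual drainage. If it is related to death, treat it as time-dependent from the first procedure, or use a landmark.
3. State that the nonresectable decompression cohort contains every patient with an attempted decompression, whatever the result.
4. Do not present eventual drainage against the Table 2 standard, which keeps its own wording and is computed from the first procedure.

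The cost is small: a reworded footnote and a change in which report is used. Table 2 already needs the first procedure's result, so no extra patients or follow-up are required. The drawback is that the first-attempt rate will be lower and will not credit planned staged drainage; the separate eventual measure covers that.

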**Patient survival after biliary decompression in palliative disease**		
	7 days [19,20]	>90
	30 days [21]	>75
Ability to proceed to palliative chemotherapy in patients with unresectable malignancy [22]		25

^a^RICOCHET: Receipt of Curative Resection or Palliative Care for Hepatopancreaticobiliary Tumours.

### Case Identification, Inclusion, and Follow-Up

Aspects of health care in the United Kingdom are modelled on a hub-and-spoke design, which arranges service delivery assets into a network consisting of a tertiary care provider, the hub, complemented by secondary care providers, the spokes. The hub offers a specialist service, including resection, whereas the spokes offer a more limited service, routing patients needing specialist treatment to the hub [23].

Adult patients with a newly suspected HPB malignancy will be identified and screened for inclusion at participating sites over a 90-day, case-identification period. A patient will be included according to one of the three inclusion criteria: (1) suspected malignant pancreatic lesion, (2) suspected periampullary lesion, or (3) suspected malignant biliary obstruction caused by a primary malignancy of the liver hilum or extrahepatic biliary tree (see Figure 1). Exclusion criteria include the following: less than 16 years of age, recurrent HPB malignancy, suspected secondary malignancy (ie, metastatic disease of an origin outside of the HPB anatomical area), and gallbladder or intrahepatic lesions. Cases will be identified at four nodes: MDT meetings, CNS referrals, from biliary decompression lists, and any remaining modes of referral, including through outpatient clinic and ward referrals (see Figure 2). Upon inclusion to the study, each patient’s management and investigative pathways will be charted from their initial relevant presentation to hospital care at the participating site. This *day zero* will be defined as the chronologically primary relevant attendance to the emergency department, outpatient clinic, discussion of the case at MDT where a diagnosis of malignancy was first considered, or the date of the radiological or endoscopic imaging that identifies an incidental finding of malignancy. Cases will be mapped by the outcome measures described in Table 1 for 90 days from *day zero*. For cases in which a patient’s care is moved between a spoke and hub center, data will be collected from site-specific *day zero* for the following 90 days. For the purpose of analysis, we will primarily assess 90-day outcomes from the first *day zero*. However, we may explore extended time points as part of an exploratory outcome analysis. The differences in treatment and outcomes of patients across centers (ie, hub or spoke) will be analyzed.

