**Methods:**

The RICOCHET study is a nationwide, multicenter, prospective study. It is led by trainees through collaboration between surgical and medical specialties. Patients with suspected pancreatic cancer, other periampullary cancer, or extrahepatic cholangiocarcinoma presenting to hospitals in the United Kingdom will be identified over 90 days. Each case will be followed up for 90 days to collect data on the mode of presentation, investigations, interventions, use of local and specialist multidisciplinary team meetings, and transfer of care between hub and spoke sites. Furthermore, the study will define dates and intervals between key points in the patient pathway.

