	**Management pathway domains**			
		Presentation to secondary care		Presentation to outpatient clinic, emergency admission, referral from spoke center, incidental radiological finding, etc
		Principal care point		Whether first presentation was at a hub or spoke center^b^
		Utility of MDT^c^		Whether case discussed at MDT meeting Timing with reference to presentation and frequency

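### Entry is by identification in a 90-day period, but the outcome clock starts at a day zero that need not fall in it, so delayed and length-biased entry is possible

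*Protocol article*

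**What the plan says.** All the relevant rules are in the protocol article, Methods, Case Identification, Inclusion, and Follow-Up.

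- **Entry.** "Adult patients with a newly suspected HPB malignancy will be identified and screened for inclusion at participating sites over a 90-day, case-identification period". Detection is at several points in the pathway: "Cases will be identified at four nodes: MDT meetings, CNS referrals, from biliary decompression lists, and any remaining modes of referral". The sentence goes on to name outpatient clinic and ward referrals under the last node.
- **Clock.** Once a patient is included, "pathways will be charted from their initial relevant presentation to hospital care at the participating site". Day zero "will be defined as the chronologically primary relevant attendance to the emergency department, outpatient clinic, discussion of the case at MDT" where malignancy was first considered, or the date of imaging with an incidental finding.
- **Follow-up.** "Cases will be mapped by the outcome measures described in Table 1 for 90 days from" day zero. A patient who moves between spoke and hub has a day zero at each site, and the primary 90-day outcomes run from the first of these.

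The section gives no calendar limit for day zero and does not define newly suspected. Recurrent malignancy is a separate exclusion. Table 1 records MDT use as "Timing with reference to presentation and frequency", so more than one MDT discussion per patient is expected.

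**The concern.** Entry and the time origin are two different events. A patient has to survive from the origin (day zero) to entry (identification at a node in the period) to be counted, yet the primary outcomes are measured from the origin. Followed as written, this is delayed entry with no allowance for left truncation.

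The clearest route is a transfer. Two patients present at the same spoke on the same day before the period opens. One is transferred, is first identified at the hub during the period, and enters with a clock set back to the spoke. The other dies before transfer and cannot enter. If a patient already known before the period may also enter at a later MDT, CNS referral or decompression list, the chance of capture grows with the time spent in the pathway.

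The primary objective is to describe pathways and 90-day outcomes, and the Discussion itself points to a "remarkably high 30-day mortality rate among patients with malignant biliary obstruction". Loss of early deaths would bear on that question directly. The planned hub/spoke comparison is exposed as well, because capture through transfer need not work equally for the two groups.

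**Working it through.** **The plan's own figure.** Sample Size projects about 1835 cases from 75% coverage, 90 days and annual incidence. The incidence is not given, so the figure can only be solved backwards: 1835 / 0.75 / (90/365) = 9,923 cases per year. It can be neither confirmed nor refuted. It is, however, a count of incident cases, which the entry rule does not secure.

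**Capture interval.** If any node in the period admits a patient, and L is the number of days from first to last node (gaps of at most 90 days), the patient can be caught over 90 + L days:

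| L (days) | Capture interval (days) | Relative to L = 0 |
|---|---|---|
| 0 | 90 | 1.00 |
| 14 | 104 | 1.16 |
| 30 | 120 | 1.33 |
| 60 | 150 | 1.67 |
| 90 | 180 | 2.00 |

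If only the first node admits a patient, every patient who reaches a node has the same 90 days.

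**Effect on mortality.** The article gives no survival from day zero, node delays or node spans, so all of these are assumed:

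- steady arrivals and exponential survival, with 30-day survival of 75% (varied to 90%). The 75% is borrowed as an anchor from the Table 2 standard after palliative decompression, which is not survival from day zero;
- exponential delay from day zero to first node, mean m = 0 to 14 days;
- three nodes, mean span 14 to 60 days.

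*First node only.* The daily hazard is λ = -ln(0.75)/30 = 0.00959. The chance of reaching the first node alive is P = 1/(1 + λm). Observed 30-day mortality is 1 - [0.75(1 - e^(-30/m)) + P × 0.75 × e^(-30/m)] / P.

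- m = 0: 25%
- m = 3: P = 0.972, reads as 22.8%
- m = 7: P = 0.937, reads as 20.0%
- m = 14: P = 0.882, reads as 16.1%

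*Any node (simulation).*

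- With m = 7 and span 30, 30-day mortality of 25% reads as 17%, 90-day mortality of 58% reads as 52%, and 25% of entrants have a day zero before the period.
- Over the whole grid, 25% reads as 12-24%.
- With 90% survival, 10% reads as 4-9%.

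**Effect on pathway length.** In the same any-node model, the mean scheduled time from day zero to last node moves less, and not always upwards:

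- 60.1 days reads as 66.6 (90% survival, m = 0, span 60);
- 37.0 reads as 39.8 (90% survival, m = 7, span 30);
- 44.0 reads as 44.3 (75% survival, m = 14, span 30);
- 27.9 reads as 27.0 (75% survival, m = 14, span 14).

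**What a date filter alone does.** With 75% survival and m = 7, requiring day zero in the period removes the over-sampling, but 30-day mortality still reads as about 20%. Deaths before any node remain unseen.

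**The case against.** The strongest reply is that newly suspected already means first suspected during the period. Recurrences have their own exclusion, so the word newly would otherwise add nothing, and the sample size counts incident cases. On that reading nobody enters at a second or later node, and long pathways after identification are not over-sampled. This stands as a possible reading, but the term is undefined. It does not clearly exclude a transferred patient first identified at the hub, and deaths between day zero and the first node are missed either way.

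The fourth node takes all other referrals, and an outpatient visit or MDT discussion can itself be day zero. For those patients the delay may be nil. This also stands, and it is why the ranges above reach up to or close to 25%. It does not guarantee capture: the emergency department can set day zero but is not named as a node.

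The 7- and 30-day survival standards in Table 2 run from decompression, and decompression lists are a node. Patients caught on those lists enter at that standard's own origin, so these standards are less exposed than outcomes counted from day zero.

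A reader might infer that the Abstract contradicts the Methods. It does not clearly do so: in "presenting to hospitals in the United Kingdom will be identified over 90 days" the 90 days attach to identification, as they do in the Methods. Nor does MDT frequency in Table 1 show that patients enter at repeat meetings; it is an outcome measure. Finally, Figure 2 is not shown and the article condenses a fuller protocol, so a date rule may exist there.

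**Conclusion.** The point holds as a design weakness whose bias is possible but not established. The article ties entry to identification and the primary clock to the first day zero across sites, and nothing in it keeps the second inside the period of the first.

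Under-sampling of early deaths follows on either reading of the entry rule whenever there is a delay between day zero and the first node. Over-sampling of long pathways needs the wider reading, in which a later node can admit a patient. It would go too far to say that survivors and long pathways *are* over-sampled, or to put one figure on it.

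The ranges given for a true 30-day mortality of 25% (about 12-24% for any node, 16-25% for first node only) rest on exponential survival and on assumed delays and spans. They show a direction and a plausible scale for mortality, and are not estimates for this study. For interval lengths the shift is smaller and its direction less certain. The correction is worth making because it rests mainly on dates and is cheap.

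**What to change.** 1. Define the primary analysis cohort as patients whose first day zero, across linked records, falls within the 90-day period, and define newly suspected to match.
2. Keep the nodes open for a fixed, pre-stated run-out after the period closes. Otherwise the date filter drops patients with an in-period day zero who are identified late.
3. Record the date and node of first identification for every case.
4. Leave cases with a pre-period day zero out of the primary interval and outcome estimates, or analyse them with delayed entry at the identification date.
5. As a sensitivity analysis, apply delayed entry at the identification date to all cases, because the date filter does not recover deaths before any node. This analysis assumes that the delay to identification is unrelated to later survival, which should be stated.

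Cost: some pre-period cases are lost from the primary estimates, screening is extended for a short time, and one date is added if it is not already captured. Day-zero dates are collected already. The article reports that data collection began in April 2018, so where screening has closed the run-out would need a retrospective search of the same nodes.

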### Sample Size

The RICOCHET study aims to involve all hub and spoke centers across the United Kingdom, and we expect to reach 75% of the cases during our inclusion period. Based on the follow-up period of 90 days and the annual incidence of the included HPB malignancies in the United Kingdom, we project the inclusion of approximately 1835 cases [1].

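### MDT discussion and CNS contact are both case-finding routes and primary-objective outcomes, so the MDT and CNS proportions are open to upward bias if patients without these contacts are found less completely

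*Protocol article*

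**What the plan says.** **Case-finding.** Protocol article, Case Identification, Inclusion, and Follow-Up: "Cases will be identified at four nodes: MDT meetings, CNS referrals, from biliary decompression lists, and any remaining modes of referral". The fourth node is a catch-all: "any remaining modes of referral, including through outpatient clinic and ward referrals". Eligibility depends on the suspected lesion, not on any service contact: "A patient will be included according to one of the three inclusion criteria".

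**Outcomes.** Table 1, under the primary objective, lists "Whether case discussed at MDT meeting Timing with reference to presentation and frequency" in the management pathway domains and "Number of patients seen by a CNS" in the intention domains. For decompression the entry begins "Utility: describing indication for decompression Modality: ERCP, PTC, or other" and goes on to complications and success. It lists no rate of use across all cases. Decompression also splits the resectable patients with obstructive jaundice into two comparison groups.

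**Coverage.** Sample Size: "we expect to reach 75% of the cases during our inclusion period", with a projection of about 1835 cases. No reason is given for the cases not reached.

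**Comparisons and limitations.** Hub and spoke are to be compared. The limitations in the Discussion cover length of follow-up and the absence of quality-of-life and patient-reported outcomes. They do not mention how cases are ascertained.

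**The concern.** A patient discussed at an MDT meeting can be found from the MDT list or from any other node. A patient never discussed can be found only from the other nodes. The same holds for CNS referral, which is closely tied to being seen by a CNS though not identical to it. When capture is incomplete, this extra route tends to over-represent patients who had the contact, and the cohort proportion with the contact then exceeds the proportion among all eligible patients.

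Describing pathway use and its variation is the study's main purpose, so the level of these proportions matters. Comparisons matter too. Node yield may differ between hubs and spokes even under one procedure; Table 1 itself treats the availability of decompression services as something to compare between them. A difference in case-finding could then be read as a difference in practice.

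**Working it through.** **Inputs from the article:** expected capture c = 0.75; projected cases N = 1835. The article gives no capture by node and no expected MDT or CNS rate, so every rate below is an assumption used for illustration.

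**1. The plan's own figure.** The annual incidence behind N is cited but not printed, so N can only be worked backwards:
- implied cases in 90 days: 1835 / 0.75 = 2447
- not reached: 2447 − 1835 = 612
- implied annual cases: 2447 × 365/90 ≈ 9,923

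**2. Bias formula.** Let p be the true proportion with the contact, s1 the capture probability of patients with it, and s0 that of patients without it.

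observed = p·s1 / [p·s1 + (1 − p)·s0]

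If s1 = s0, observed = p and there is no bias.

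**3. Upper limit at 75% overall capture.** Fixing p·s1 + (1 − p)·s0 = 0.75 gives observed = p·s1 / 0.75. Since s1 ≤ 1, observed/p ≤ 1/0.75 = 1.33. For p above 75% the limit is tighter, because the observed rate cannot exceed 100%.

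| True p | s1 | s0 = (0.75 − p·s1)/(1 − p) | Observed = p·s1/0.75 |
|---|---|---|---|
| 50% | 0.75 | 0.75 | 50% |
| 50% | 0.90 | 0.60 | 60% |
| 50% | 1.00 | 0.50 | 67% |
| 70% | 0.75 | 0.75 | 70% |
| 70% | 0.90 | 0.40 | 84% |
| 70% | 1.00 | 0.17 | 93% |

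**4. From an observed rate back to the true rate.** With 25% missed and nothing known about them, the true rate lies between 0.75·o and 0.75·o + 0.25:
- observed 80%: 60% to 85%
- observed 90%: 67.5% to 92.5%

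These are extreme bounds, and they also allow a true rate above the observed one. The expectation of an upward bias comes from the extra route, not from this arithmetic.

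**5. Dependence on the catch-all node.** Suppose every patient with the contact is found (s1 = 1), the true rate is 80%, and a fraction k of the others is found. Then observed = 0.80 / (0.80 + 0.20k):
- k = 100%: 80%
- k = 75%: 84%
- k = 50%: 89%

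In the last case capture is 0.80 + 0.20 × 0.50 = 90%. If that were capture within participating centers, those centers would need to hold 0.75/0.90 = 83% of all cases to give 75% overall. Two groups with the same true 80%, one with k = 100% and the other with k = 50%, would differ by about 9 percentage points through case-finding alone.

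**The case against.** The strongest reply is that the catch-all node exists for this purpose. It covers clinic and ward referrals, and eligibility requires no service contact. A patient managed on a ward without MDT or CNS input can enter through it, and if it works as well as the other nodes the bias is zero. This stands: the bias is a conditional risk. It does not remove the risk, because the node still depends on some form of referral and the article describes no check on how complete it is.

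Four stronger readings are tempting, and the article does not support them.
- *The missed quarter are mainly patients without the care being measured.* No reason is given for the shortfall. The study aims to involve all centers but speaks of up to 227 sites, so centers that do not take part may explain some or all of it. Such losses need not bias rates within participating centers.
- *Decompression rates are inflated.* Table 1 lists no overall decompression rate. The complication and success measures and the decompression audit standards concern patients already decompressed, so entry through a decompression list does not directly inflate them.
- *A site searching only MDT lists would show nearly 100% discussion.* The Data Collection section requires the same case-finding at every site. Uneven yield across nodes is the realistic worry.
- *The plan fails to record the identifying node.* Figure 2 is not visible, and an article leaves such form detail to the full protocol. If the node is already recorded, only the analysis and the label remain to be added.

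**Conclusion.** The point holds for MDT and CNS as a risk of upward bias that the stated plan does not check or acknowledge. Its size cannot be derived from the article: it runs from zero, under equal capture, to a factor of at most 1.33 at 75% overall capture. It is smaller to the extent that the missing 25% comes from non-participating centers. A reader might infer that the rates are certainly inflated; that would require evidence, absent here, that the fourth node under-captures.

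For decompression the concern is confined to the resectable patients with obstructive jaundice. The decompressed have a route into the sample that the others lack, so the non-decompressed group may be a less complete selection of its kind.

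The conclusion rests on two assumptions: that capture within participating centers is incomplete, and that the extra route raises the chance of being found. The study's value is not in doubt, but the correction is cheap and worth making.

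**What to change.** 1. Record in REDCap, as a multi-select field, every node at which each case appeared. This must include clinic and ward referral for cases already found elsewhere. If the fourth node is kept only for cases found nowhere else, it will exclude MDT- and CNS-listed patients by construction and will push the restricted estimates down.
2. As a sensitivity analysis beside the crude rates, report the MDT proportion among cases found at any non-MDT node and the CNS proportion among cases found at any non-CNS node, overall and for hub versus spoke.
3. Label the crude rates *among identified cases*, and name ascertainment through these contacts as a limitation.
4. For the comparison of decompressed with non-decompressed patients, show the mix of nodes in each group.

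Two further analyses are not advised. Per-site capture-recapture has too few cases: 1835/227 is about 8 per site if all sites take part. A decompression rate among cases off the decompression list would tend to zero by construction.

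**Cost:** one data field and one secondary analysis. The restricted estimates use fewer cases, so they are less precise. They also assume reasonable independence between nodes: if patients referred to a CNS are also more often discussed at MDT, some upward bias remains.
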